## Abstract

**Introduction:**

Dizziness is a common symptom that can occur in an unpredictable and episodic manner leading to the imprecise reporting of symptoms. Patients will often see many specialists before receiving a diagnosis and treatments can vary in terms of risk and invasiveness which places a significant burden on health services. Achieving an early precise diagnosis could be key in reducing the impact of symptoms on patients and health services.

**Methods and analysis:**

The continuous ambulatory vestibular assessment (CAVA) trial is a single-arm, non-randomised, multicentre diagnostic accuracy device trial that aims to quantify the extent to which the CAVA system can differentiate three common inner-ear causes of dizziness: Ménière’s disease, vestibular migraine and benign paroxysmal positional vertigo. 85 participants with an established diagnosis from each of the three dizziness conditions, a total of 255 participants, will be recruited from ear, nose and throat, audiology and audiovestibular medicine departments in National Health Service (NHS) sites across the UK. The CAVA device is composed of two components: A set of bespoke single-use sensor arrays that adhere to the left and right side of the participant’s face; and a small reusable module fitting over the ear that contains a battery, a data storage facility and connection ports for the arrays. The CAVA device will be worn by all participants for up to 30 days with the aim of capturing eye movement data during a dizzy attack. The first objective is to develop an algorithm that can discriminate between the three dizziness conditions listed above. The second is to quantify the financial and patient benefits of deployment in the NHS. The final objective is to expedite a plan to deploy the system in the NHS.

**Ethics and dissemination:**

The trial was approved by the West Midlands—South Birmingham Research Ethics Committee and the Medicines and Healthcare products Regulatory Agency (MHRA). REC reference: 22/WM/0229, IRAS Project ID: 317899, and MHRA: CI/2022/0062 /GB. Participants will provide full informed consent and can withdraw for any reason without it affecting their standard care. Dissemination will include publication in peer-reviewed journals, presentations at academic and public conferences including patients and the public and to policymakers and practitioners.

**Trial registration number:**

ISRCTN81218533, trial protocol V.3.1 (25 January 2024).

Strengths and limitations of this studyThe continuous ambulatory vestibular assessment (CAVA) system is novel in that it records horizontal and vertical eye movements and head accelerations 24/7 and analysis of these signals when they correspond to dizziness symptoms will allow clinicians to retrospectively evaluate the attacks through review of the data.A large number of subjects recruited from centres all over the country will enable the collection of a considerable amount of data for training an artificial intelligence system to diagnose the three conditions listed.The device is technically reliable, comfortable to wear and easy to apply and remove.The CAVA system relies on the patient experiencing an episode of dizziness while wearing the device.The trial is limited to the diagnosis of the three index conditions: Ménière’s disease, vestibular migraine and benign paroxysmal positional vertigo.

## Introduction

 Up to 30% of the general population have experienced dizziness significant enough to interfere with activities at some point over their lifetime.^1^ Dizziness can have many causes and it can often present in an episodic manner and frequently unpredictable, so patients present as ‘normal’ during examination interictally; furthermore, reporting of symptoms is imprecise.^2 3^ Although many balance tests are available, they only provide a snapshot of balance function in the absence of an acute attack.^2^ Patients will see up to five specialists before receiving a diagnosis^4^ and the treatments offered vary in terms of risk and invasiveness. Dizziness places a significant burden on health services.^5^

Dizziness is debilitating. The three most common causes of episodic vertigo include Ménière’s disease (MD), vestibular migraine (VM) and benign paroxysmal positional vertigo (BPPV). MD and VM are conditions which result in unpredictable and violent episodes of extreme rotational vertigo, lasting for several hours. Patients with BPPV experience shorter episodes, provoked by normal movement of the head such as with looking up. Dizzy attacks can cause patients to vomit and will leave them physically exhausted. It can take weeks to recover in full, making everyday activities impossible. Dizziness has a financial impact on patients taking frequent sick leave from work or time off to attend hospital appointments.^6^

Different treatment options are available for the three conditions of interest. Patients with MD may be treated with invasive injections into the middle ear which carry risk of infection, damage to the eardrum and hearing loss. Drugs for VM are not without risk and the process of identifying the correct drug is time-consuming. By contrast, BPPV is treated by a simple head manoeuvre, however, if the manoeuvre is done on a patient with an incorrect diagnosis it is likely to result in repeated and unpleasant symptom provocation without benefit. Delays before receiving the correct diagnosis and treatment prolong the suffering of patients, both in terms of the dizziness itself as well as the uncertainty of their prognosis and when the diagnosis is unclear patients may be offered treatments which are eventually revealed to have been for the incorrect condition. Therefore, there is a benefit in providing quick access to the correct condition-specific treatment.

The relationship between balance and eye movements known as the vestibulo-ocular reflex stabilises images on the retina during head movement. When a malfunction occurs in the pathway involving the ears, eyes and brain, an abnormal eye movement is produced, known as nystagmus.^7^ This is characterised by drifting of the eyes in one direction followed by a corrective rapid flick of the eyes in the opposite direction. Different diseases produce different patterns of nystagmus, for example, predominantly horizontal (peripheral vestibular nystagmus), predominantly torsional (BPPV), predominantly vertical (causes outside the peripheral vestibular system).^8^,^10^ The ability to characterise nystagmus will allow us to differentiate between the various vestibular causes of a ‘dizzy attack’ and in the future may provide insights into mechanisms underlying other disorders.

CAVA (continuous ambulatory vestibular assessment) is a wearable device developed to detect nystagmus. As some dizziness can be provoked by the movement of the head,^11^ the CAVA device also records the movement of the head in three axes. The eye movement data captured by the CAVA device is a critical parameter for assessing patients with dizziness.

The CAVA system was evaluated during a clinical investigation involving 17 healthy volunteers. Algorithms were developed to detect physiologically induced nystagmus and achieved an extremely high degree of sensitivity and specificity.^12^ The device was technically reliable, patients were happy to wear it and it was safe.^13^ Participants found the device to be easy to apply and remove and found it to be comfortable to wear. They had little difficulty sleeping while wearing the device and reported that it did not interfere greatly with their daily activities. They did not feel self-conscious wearing the device. From the initial proof-of-concept prototypes, the CAVA device was designed and confirmed to record maximum ocular excursions and eye movements as small as 5 degrees. These tests took place on several subjects with different head shapes, ensuring that recording was not limited by physiological differences or by placement on the face.

Previous approaches to record vertigo attacks include: (1) Wolf described a portable device for recording two channels of eye movement to a floppy disk for 10 minutes.^14^ This system did not allow for continuous monitoring and is now technologically obsolete. (2) Rauch proposed an ambulatory device for recording physiological parameters including ECG, respiration rate, skin temperature, head and eye movement.^15^—this device is no longer in development. (3) Young used video cameras mounted in swimming goggles to record the eyes but patients close their eyes during attacks and attacks can start during sleep.^16^ Wolf’s and Young’s systems are applied at the onset of vertigo which is challenging for attacks that begin without warning. The CAVA system overcomes these limitations and has been proven to be effective in previous research.

During our most recent clinical investigation (NCT04026516), the device recorded the first-ever full example of an acute attack of MD revealing a novel period of nystagmus preceding a full attack.^17^ The data from the CAVA device has allowed a greater insight into the symptoms reported by individuals with an otherwise identical history.^18^ We have also confirmed that a variety of nystagmus signals exhibiting different characteristics can be identified reliably from the data recorded for which we developed novel artificial intelligence (AI) techniques.^12 17 19^

We have completed proof-of-concept work showing that the CAVA system provides information to allow our target diseases to be differentiated by way of five parameters: Nystagmus duration, whether the nystagmus changes direction, the slow phase velocities (speed of the drifting motion), the nystagmus slow phase duration and whether the nystagmus is motion-provoked.^20^ These findings are supported by Young *et al*.^16^ The next step is to demonstrate the consistency of these findings among a larger group of patients to develop algorithms to automatically discriminate these conditions and to determine their diagnostic accuracy.

### Aims and objectives

We will develop the CAVA system’s capabilities from detecting nystagmus to diagnosis based on the novel, long-term data it records. This work is supported by our proof-of-concept data showing that our objectives are feasible. We will demonstrate the potential economic and patient benefits offered by the device and instigate a plan to deploy the system into the National Health Service (NHS).

Aim: Establish to what extent the data from the CAVA system can be used to differentiate three of the most common inner-ear causes of dizziness.

Primary Objective: Enable the CAVA system to differentiate between MD, VM and BPPV.

Objective 2: Quantify the health and economic benefits of an alternative diagnostic pathway involving the CAVA system.

Objective 3: Finalise and instigate a project-exit plan to deploy the CAVA system into general clinical use in the UK publicly funded healthcare systems, the NHS and internationally.

## Methods and analysis

### Trial design

This is a single-arm, non-randomised multicentre diagnostic accuracy study using a medical device including an assessment of health economics and the formation of a commercialisation plan.

### Study setting

Participant recruitment will be from ear, nose and throat (ENT) departments, audiology departments and departments of audiovestibular medicine in NHS institutions distributed across sites in the UK ensuring a broad diversity of participants in terms of gender, age, socioeconomic group and ethnicity.

### Patient and public involvement

Three volunteers with dizziness conditions have been involved in early testing of the device, development of trial materials and are included as members of our trial management groups (TMGs) and steering committee to advise on study progress and dissemination. A separate patient and public involvement event with individuals with dizziness conditions was held to gain feedback on the acceptability of the device and trial processes.

### Population

We will seek patients with a confirmed diagnosis of one of the three conditions of interest (unilateral MD,^21^ VM,^22^ unilateral posterior canal BPPV^23^ currently experiencing symptoms within 4 weeks prior to recruitment.

Inclusion criteria:

Age 18 and over.Must have relevant index medical condition: Meniere’s: MD, VM, posterior canal BPPV.Experiencing episodes of true vertigo with at least two episodes within the preceding 4 weeks at the time of consent.The vertigo is of a duration and a nature supportive of the relevant index medical condition.It is advisable that participants have access to a phone so they can contact the research team with any issues.Willing to provide informed consent.Willing to comply with the study protocol for using the CAVA device.Willing to complete all study materials.Adequate grasp of the English language or language used within an existing translated version of the informed consent form and patient information sheet and where hospital translators are available to provide support.

Exclusion criteria:

Has an allergy to plasters and/or medical adhesives.Evidence of dermatitis, fragile skin or any other condition that could be aggravated by the repeated application of skin surface adhesives.Pregnant or breastfeeding mothers.Bilateral or second side MD.Active bilateral or second-side posterior canal BPPV.Currently enrolled on an intervention trial (not including questionnaire-based or observational trial).Patients who meet diagnostic criteria for more than one eligible condition at the time of recruitment.

### Recruitment and screening

255 participants, 85 per target disease, will be recruited from ENT departments, audiology departments and departments of audiovestibular medicine through NHS hospitals. Up to a total of 400 participants may be recruited in order that up to 30 days of data (and/or at least one qualifying dizziness attack with nystagmus) from the device is collected from 255 individuals.

Potential participants will be identified by staff familiar with the trial and the relevant departments in NHS institutions in the UK. Posters will also be used to inform participants of the trial.

Potential participants will be provided with study information either in person or by post/email. They may also be contacted by phone or they may contact the clinical research team directly. All potential participants will be offered the opportunity to discuss the advantages and disadvantages of study participation with a member of the research team and/or their physician before providing consent. See online supplemental materials for a copy of the participant consent form.

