### Intervention

All participants fulfilling the eligibility criteria and providing consent will wear the CAVA device for up to 30 days. To balance the consequences of delaying BPPV treatment with not being able to identify the nystagmus associated with BPPV, individuals with BPPV will be offered a particle positioning manoeuvre after 4 days of wear. The CAVA algorithm will then diagnose each patient based only on the data recorded from the device. The accuracy of the system will be tested by comparing the CAVA system’s diagnosis with each patient’s known diagnosis. The results of the algorithm work (‘the diagnosis’) will not be available until the end of the trial and will not be made available to clinicians or patients during the trial.

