### Sample size

A minimum sample size of 85 participants for each of the three conditions is required to demonstrate a minimum diagnostic sensitivity of 95% and a specificity of 95% with a 3% margin of error for each condition.

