### Retention

The trial intervention period is relatively short, so retention is not expected to be too challenging. It is anticipated that some participants will not wear the CAVA device or have a dizziness attack while wearing the device within 30 days, so the sample size is inflated to allow for this. Some non-conformance will be apparent or self-reported by the participant, others will only be detected once the data is downloaded at the end of the 30 days. Therefore, recruitment will continue until the device data analysis team confirms 255 participants with one qualifying dizziness event or the maximum upper approved limit of 400 participants is reached.

A potential challenge with retention is participants who drop out not returning the CAVA device. As this could impact the rest of the trial, participants are offered a £20 voucher incentive on return of the device and electrodes.

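### The rule for who counts toward 255 differs between two sections and is set on the total, so recruitment can end with fewer than 85 evaluable participants in a condition

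*Protocol article*

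**What the plan says.** Four statements in the protocol article bear on this.

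- Sample size sets the requirement by condition: "A minimum sample size of 85 participants for each of the three conditions is required", to show "a minimum diagnostic sensitivity of 95% and a specificity of 95% with a 3% margin of error for each condition".
- Recruitment and screening gives the split for those recruited: "255 participants, 85 per target disease, will be recruited". It then allows up to 400 so that "up to 30 days of data (and/or at least one qualifying dizziness attack with nystagmus) from the device is collected from 255 individuals".
- Retention gives the rule for ending recruitment: "recruitment will continue until the device data analysis team confirms 255 participants with one qualifying dizziness event", or until "the maximum upper approved limit of 400 participants is reached". The stated reason for the inflation is that "some participants will not wear the CAVA device or have a dizziness attack while wearing the device within 30 days".
- Intervention describes one feature that applies to a single condition: "individuals with BPPV will be offered a particle positioning manoeuvre after 4 days of wear".

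Data analysis adds that the diagnostic algorithm is trained on nystagmus waveforms labelled with the patient's diagnosis, and tested by leaving out one subject at a time.

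**The concern.** There are two faults.

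**The counting rules differ.** The *and/or* in Recruitment and screening lets a participant who wore the device but had no attack count toward 255. Retention does not count that participant, and names the absence of an attack as a reason for recruiting more people. A team keeping the tally cannot follow both sections.

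**The target is a total, while the requirement is by condition.** Neither statement about the evaluable 255 repeats the split of 85. Once up to 400 may be recruited, 85 recruited in a condition no longer means 85 evaluable in it, and a surplus in one condition can hide a deficit in another.

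The precision of sensitivity for each condition is at stake, because that estimate rests only on the participants with the condition who supply a waveform to classify.

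**Working it through.** **The plan's own figures.** 3 × 85 = 255 holds. The cap gives 255/400 = 0.6375, so it absorbs an overall loss of up to 36.25%. The figure of 85 is not reproduced by the usual precision formula n = z²p(1−p)/d² with p = 0.95 and d = 0.03. That gives 203 at 95% confidence, 143 at 90% and 87 at 80%, and the article states no confidence level. This is a separate matter. Below, 85 is taken as the plan's requirement.

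**Who counts under each section:**

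| Participant | Recruitment and screening | Retention |
|---|---|---|
| Wear data, no attack | counts (through *or*) | does not count |
| Qualifying attack with nystagmus | counts | counts |

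**Effect of a total-only stop (Retention rule).** The evaluable rates r are assumptions, because the article gives none. With equal recruitment, recruits at the stop are N = 255 / mean(r), limited to 400, and the evaluable number in a condition is (N/3) × r.

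| Assumed rates | Recruits at stop | Evaluable by condition |
|---|---|---|
| 0.8 / 0.8 / 0.8 | 319 | 85 / 85 / 85 |
| 0.9 / 0.9 / 0.5 | 333 | 100 / 100 / 55 |
| 0.8 / 0.8 / 0.4 | 382 | 102 / 102 / 51 |
| 0.7 / 0.7 / 0.5 | 400 (cap) | 93 / 93 / 67 |

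For the second row, mean(r) = 2.3/3 = 0.767, 255/0.767 = 333, and 333/3 = 111 per condition. Then 111 × 0.9 ≈ 100 and 111 × 0.5 ≈ 55.

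Unequal rates are not needed for some imbalance. If the 255 fall at random with equal expected shares and no quota, the chance of exactly 85/85/85 is about 0.003. The smallest group then has a median of 78 and a 5th percentile of 69.

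**Effect of the looser count.** Suppose, at the extreme, that every recruit returns data and so counts. Recruitment then stops at 255, or 85 per condition. At 0.9/0.9/0.5 the evaluable numbers are 85 × 0.9 = 76.5 in two conditions and 85 × 0.5 = 42.5 in the third.

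**Precision lost.** The 95% half-width at 95% sensitivity is 1.96 × √(0.05 × 0.95/n): 4.6 points at n = 85, 4.8 at 78, 5.1 at 69, 5.8 at 55 and 6.0 at 51. The part due to this fault is the increase over 4.6, which is 1.2 points in the 0.9/0.9/0.5 example.

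**With closure by condition.** Recruits needed are 85/r, rounded up. At 0.9/0.9/0.5 this is 95 + 95 + 170 = 360, within the cap. At 0.8/0.8/0.4 it is 107 + 107 + 213 = 427, above the cap. If the first two conditions close at 107, then 400 − 214 = 186 places remain, giving about 186 × 0.4 = 74 evaluable in the third, against 51 under the total-only stop.

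**The case against.** The strongest reply is that 255 is shorthand for 85 in each condition. Recruitment and screening opens with that split, the Abstract gives it too, and Sample size repeats the minimum. Nothing says that the mix may float, and the full clinical investigation plan, which is not shown, may hold quotas. This is a fair account of the probable intent. But the split is attached to participants recruited, and neither statement about the evaluable 255 carries it over.

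It can also be said that Recruitment and screening explains the purpose of the 400 and that only Retention sets a stopping rule. The word *qualifying* in Retention may also carry the nystagmus requirement with it. Both readings are plausible, so the clear discrepancy is the *and/or*. Quotas elsewhere would not remove it.

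A reader might infer three stronger claims, which the article does not support:

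- *Attack-free recordings are useless.* They supply no waveform for the diagnostic classifier, but the primary outcome as worded is nystagmus identification with sensitivity and specificity. Specificity there needs nystagmus-free signal, and compliance and safety also use such recordings.
- *BPPV will fall short.* Only BPPV has a manoeuvre offered after 4 days, so a shortfall there is possible. But no capture rate is given, the manoeuvre is only offered, wear may continue to 30 days, and the Introduction describes BPPV episodes as provoked by ordinary head movement. A constant-rate model at the eligibility minimum, with no capture after day 4, would rest on assumptions that the article does not make.
- *This fault explains the gap to the stated 3-point margin.* At n = 85 the 95% half-width is already 4.6 points.

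**Conclusion.** The concern holds as a conflict of wording and a target set at the wrong level. As written, attack-free participants may count toward 255 under Recruitment and screening, and under either section recruitment may end at 255 with one condition below 85. The size depends on evaluable rates that the article does not give. In the illustrations of a total-only stop with unequal rates, the smallest condition has 51 to 67 evaluable participants instead of 85. With equal rates in every condition, the expected split is 85 each and only chance imbalance remains. No claim is made about which condition would be short, and the manoeuvre in BPPV is not in question.

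**What to change.** Use one definition of an evaluable participant in Recruitment and screening and in Retention: at least one recorded qualifying attack with nystagmus confirmed by the device data analysis team. Delete *and/or*. Close recruitment to each condition when 85 such participants are confirmed in it, or to all conditions when 400 have been recruited overall. If the cap comes first, report the achieved number and precision for each condition. Keep attack-free recordings for nystagmus-detection specificity, compliance and safety, without counting them toward the 85.

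The cost is a wording change in two sections and a running count by condition. One condition may stay open longer than the others, and total recruitment may be higher than under a total-only stop: about 360 rather than 333 in the main example, though never above the approved 400. At low rates the cap may still be reached before 85, which is why the reporting clause is needed.
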